#### The program at the inpatient clinic

Three interdisciplinary teams are working with the RTW program at the clinic. Each team consists of a physician, a physiotherapist/psychomotor physiotherapist, a psychologist or a nurse, an occupational work consultant, and a sports pedagogue. One of them has the role of team coordinator. All teams and their patients also have access to a nutrition counselor, a riding instructor, and recreational instructors. Seventeen patients arrive at the clinic at the same time and stay for four consecutive weeks (36 h/week). The physician reads all the information in the referral papers sent from the patient’s general practitioner. In collaboration with the team, it is decided which team members will perform the first mapping conversation with the patient and who will be the coordinator during the patient’s stay at the clinic. The coordinator is responsible for a weekly meeting with the patient and decides whether the patient needs an individual therapeutic conversation with any of the other team members. The coordinator also contacts the employer and/or NAV. The team coordinates its activities and discusses approaches in regular team meetings. Individual goal setting and RTW planning are organized as a process in six group meetings during the stay. Visual tools are also used at the outpatient clinic to stimulate dialogue about the patient’s challenges and resources in the RTW process. The main part of the program is group-based physical activities such as gym, water exercise, psychomotor physiotherapy, climbing, Nordic walking, and other outdoor activities, which are led by sports pedagogues or physiotherapists. Different team members also give educational sessions in groups. The sessions cover themes such as the connection between bodily and psychological reactions, pain management, physical activity and training, introduction to mindfulness, diet and nutrition, and rights and responsibilities as an employee on sick leave. Communication with the patient’s employer and NAV consultant is usually done once during the stay by phone. For more details regarding the intensity of the intervention, see Table 2.

Description of the core components and intensity of the clinics, adopted from Costa-Black et al. 2013: 432 [15].

### Outcome measurements

#### Primary outcome measures

##### Return to work

*RTW* is our primary outcome measure, and it will be measured in different ways with registry data from NAV.
Cumulative number of sickness absence days. In line with Aasdahl and colleagues [55], the primary outcome measure is defined as the cumulative number of sickness absence days. By combining information from the different medical benefits, we will calculate the days on medical benefits (according to a 5-day work week) for every month during follow-up. Time on graded sick leave will be transformed into whole workdays. Days receiving sick-leave payment and work assessment allowance will be adjusted for the employment fraction, including a graded disability pension at inclusion. Any increase in the disability pension during follow-up will be counted as sick leave. The cumulative number of sickness absence days will be calculated at 6, 12, 24, and 60 months after inclusion. The evaluation of any subgroup differences will be based on this outcome.Time to stable return to previous or new work, full or partial, for at least 4 weeks without relapse. Time to RTW will be calculated as the number of calendar days measured from the start of the program until 5 years later.The proportions of workers at work full time or part-time, at baseline and every month after the start of participation in the program for 5 years.The proportion of workers who increase or decrease their work status or who have the same work status as they had at baseline. This outcome will be measured at 3, 6, 12, 24, and 60 months after baseline.Individual shifts between work, sick leave, and other social security benefits. This outcome will be monitored continuously based on registry data collected from 2 years before inclusion until 5 years after inclusion in the study [6].

To increase the external validity of the study, the RTW results for items one and two will also be compared to the results of a matched group drawn from the NAV registry.

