#### Sample size

Estimation of the sample size is based on the assumption that approximately 50% of the patients will have a stable RTW, full-time or part-time, after 1 year. A two-sided survival analysis with a 5% level of statistical significance and 80% power shows that we will be able to detect a statistically significant difference between the programs at a hazard ratio of 0,73 with a sample size of 600 participants. Due to the lower capacity at the outpatient clinic, 200 participants will be recruited from the outpatient clinic and 400 will be recruited from the inpatient clinic.

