### Outcome assessment and evaluation

Cox proportional hazard models will be used to analyze the time until stable/sustainable RTW. Analyses will be performed for both full-time and part-time RTW. If there is an imbalance in any prognostic factors for RTW and this factor is strongly correlated with the RTW outcome, analyses of differences in RTW between the two clinics will be adjusted for prognostic dissimilarities if we have sufficient power [69]. To determine the probability of RTW, sick leave, other benefits, or disability pension, a multistate model can be established [70]. This model can determine whether there are differences in the patterns of RTW if differences in the results are discovered in the overall analyses. Since the primary outcome data are based on complete registry data, missing data should not be a problem.

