### Subgroup analyses

Subgroup analyses will be performed for the primary outcome (stable/sustainable RTW). All subgroup analyses will be performed using the same analytical model as that for the primary outcome but will also include the subgroup of interest and a treatment-by-subgroup interaction [69]. Interaction tests will be considered significant at the 5% level.

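### The protocol names two different measures as primary and bases the subgroup analyses on each in turn; the stated 80% power covers only time to stable RTW.

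*Protocol article*

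**What the plan says.** All references are to the protocol article.

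- **Primary outcome measures, Return to work.** RTW "is our primary outcome measure, and it will be measured in different ways with registry data from NAV". Five measures follow. The first is singled out: "the primary outcome measure is defined as the cumulative number of sickness absence days". Its time points are fixed without a ranking: "The cumulative number of sickness absence days will be calculated at 6, 12, 24, and 60 months after inclusion". The same item ends: "The evaluation of any subgroup differences will be based on this outcome". Time to stable RTW, full or partial and lasting at least 4 weeks, is the second item.
- **Sample size.** "Estimation of the sample size is based on the assumption that approximately 50% of the patients will have a stable RTW" after 1 year. A two-sided 5% survival analysis with 80% power and 600 participants (200 outpatient, 400 inpatient) is said to detect a hazard ratio of 0.73.
- **Outcome assessment and evaluation.** "Cox proportional hazard models will be used to analyze the time until stable/sustainable RTW". An optional multistate model is mentioned for the probabilities of RTW, sick leave, other benefits and disability pension.
- **Subgroup analyses.** "Subgroup analyses will be performed for the primary outcome (stable/sustainable RTW"; and "All subgroup analyses will be performed using the same analytical model as that for the primary outcome", with a treatment-by-subgroup interaction tested at 5%.

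**The concern.** Two sections name different measures as the primary outcome, and the same two name different measures for the subgroup analyses. An analyst cannot obey both.

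The measures can rank the programs differently. A partial return that holds for 4 weeks is an event for time to stable RTW. In the cumulative count, the graded part of the absence and any later relapse keep adding days. A program that produces early partial returns with relapses could look better on the first measure and worse on the second.

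The subgroup conflict matters most. The Aims hypothesize no overall difference but benefit from one program or the other in some subgroups, so the subgroup results are a main product of the study. The economic evaluation is also conditional on a statistically significant difference in RTW rates, and that trigger is unclear while the primary measure is.

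**Working it through.** **1. The sections side by side**

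| Section | Named primary | Used for subgroups | Sized or modelled |
|---|---|---|---|
| Return to work | Cumulative absence days | Cumulative absence days | – |
| Sample size | – | – | Stable RTW, survival analysis |
| Outcome assessment and evaluation | – | – | Stable RTW, Cox model |
| Subgroup analyses | Stable/sustainable RTW | Stable/sustainable RTW | Same model as for the primary outcome |

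The first and last rows contradict each other in two columns. The subgroup model is defined by reference to the primary outcome, so it is uncertain too.

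**2. What the stated power refers to**

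Inputs from Sample size: hazard ratio 0.73, two-sided 5%, 80% power, about 50% with stable RTW at 1 year, N = 600, split 200:400.

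Schoenfeld: events D = (1.960 + 0.842)² / [p(1−p)(ln HR)²], where p is the share in one arm and (ln 0.73)² = 0.0990.

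- Equal arms: D = 7.849 / (0.25 × 0.0990) = 317, so N = 317 / 0.5 = 634. With 300 events (0.5 × 600), power is 77.8%.
- Arms 1:2: D = 7.849 / (0.2222 × 0.0990) = 357, so N = 357 / 0.5 = 714. With 300 events, power is 72.9%.

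The stated 600 is therefore approached but not reproduced exactly. At equal allocation the word *approximately* leaves room, since 317 / 600 = 53% events would suffice. The gap at 1:2 is a separate matter that this point does not need. What matters here is that the calculation is stated in event proportion and hazard ratio, so it is about time to stable RTW. Nothing in it transfers to a mean number of days.

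**3. What could be said for cumulative days**

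The document gives neither an SD nor a target difference. By the unadjusted normal approximation for two means:

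(1.960 + 0.842) × √(1/200 + 1/400) = 2.802 × 0.0866 = 0.243 SD.

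For assumed SDs of 60, 80 and 100 workdays (my assumption, not in the document) this is 14.6, 19.4 and 24.3 days.

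**4. Multiplicity, as a side issue**

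Four horizons plus Cox analyses of full-time and part-time RTW give six candidate tests. If they were independent, the chance of at least one false positive would be 1 − 0.95⁶ = 26%. They cannot be independent: each longer horizon contains the shorter ones, and the two Cox analyses share people and events. By simulation, the four nested sums alone give about 15% if increments are independent with variance proportional to time. Six tests with a common correlation of 0.5 to 0.8 give about 21% to 14%. The increments and correlations are assumptions.

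**The case against.** The strongest defence is that RTW is declared as a family of measures and time to stable RTW is its second member. The sample size and Cox model then serve a listed primary measure, and nothing foreign has been introduced. That is fair, and it rules out reading this as a switch to an unrelated endpoint. It does not remove the conflict, because the same section goes on to single out cumulative days as the primary measure and as the subgroup measure.

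A reader might infer that cumulative days will have no analysis model at all. The document does not support that. A model can sit in a statistical analysis plan that is not shown, and its absence from an article is no fault. Nor is the Cox model the only one mentioned, although the optional multistate model concerns state probabilities and not cumulative days. An analysis plan could also choose the outcome, but whichever it chose would contradict one section of the published text.

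A reader might also infer a 26% false-positive risk. That is a ceiling the overlapping tests cannot reach.

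Two mitigations stand in part. The Abstract says researchers will be blinded to group when analysing the quantitative RTW data. This limits choosing by favoured direction but not by significance, and arms of 200 and 400 may be recognisable by size. The Limitations disclaim any evaluation of significant differences in effect between the nonrandomized arms, and the Discussion acknowledges false positives in subgroup analyses. The plan nevertheless tests interactions at 5% and makes the economic evaluation depend on significance.

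**Conclusion.** The point holds as an internal contradiction and should be settled before the comparative analyses. It rests on the wording alone and needs no outside assumption: one section makes cumulative absence days primary and the subgroup basis, another does the same for stable RTW, and the sample size and Cox model follow the latter. The claimed 80% power at a hazard ratio of 0.73 therefore says nothing about the measure defined as primary in the outcome section. If cumulative days stay primary, the choice among the four horizons is also open.

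The numerical consequences are less certain. The 0.24 SD is an illustration that assumes 200 versus 400, approximate normality and no covariate adjustment. Absence days are bounded, the groups are not randomized, and the plan foresees adjustment for prognostic imbalance, so the precision achieved will differ. Some multiplicity exists, but its size depends on unknown correlations and the conclusion does not rest on it.

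**What to change.** Name one primary outcome and use it in Return to work, Sample size, Outcome assessment and evaluation, and Subgroup analyses. List the other RTW measures as secondary. Either choice works, and it is the sponsor's to make:

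- **(a) Time to stable RTW primary.** Amend the defining sentence and the subgroup sentence in Return to work. State that the primary definition is full or partial return, which is what the sample size assumes. The other sections keep their outcome and the present power basis stays. This changes least.
- **(b) Cumulative absence days primary.** Name one horizon as primary and treat the other three as supportive. Replace the bracketed outcome in Subgroup analyses. State that the power statement applies to time to stable RTW as a secondary outcome. Give a detectable difference for cumulative days with a justified SD; the 0.24 SD above shows scale only and is not a ready substitute. Outcome assessment and evaluation should name this outcome, with the model given there or in the analysis plan.

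Under either option, say which measure triggers the economic evaluation. All the RTW measures come from registry data already planned, so the cost is wording and, under (b), one calculation. Date the change and record that it was made before outcome data were compared between programs, if that is so.

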### Study setting and context

In Norway, most employees with MSDs and CMDs visit a general practitioner if they need a sick leave note. According to the National Insurance Act, they are entitled to tax-paid sickness benefits if they are incapable of working due to disease, illness, or injury [53]. Sickness benefits are paid from the first day of absence for a period of up to 52 weeks, usually at the same level as employment income. After the sick leave period, work assessment allowances or disability pensions may be granted if work ability is reduced by 50% or more. The allowances are 2/3 or less of the employment income, with a maximum duration of 3 years. Physicians may refer sick-listed employees to primary care or complex occupational rehabilitation interventions in secondary and tertiary healthcare to facilitate RTW. Complex rehabilitation programs are offered to a small number of persons who need a service that goes beyond what is delivered in primary care. The nature of these persons’ illness, the length of time they have been off work, and their circumstances at work or home often make their needs more complex [4].

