### Data collection

Quantitative and qualitative data collection methods will be used.

We will obtain registry data from NAV on work participation, sickness benefits, work assessment allowances, and disability pensions. Data regarding labor participation and employment will be collected from the State Register of Employers and Employees administered by NAV or equivalent data from Statistics Norway. Data on education will be obtained from the National Education Database (NUDB). Information about diagnoses and treatments in specialist healthcare will be collected through the Norwegian Patient Registry (NPR). The participants will be followed from 2 years before inclusion until 5 years after their inclusion in the project via their registry data.

Survey data collection will be performed at baseline, the end of the program, and 6 and 12 months after the start-up of the program.

Data on program components, services, and epicrises will be collected from the clinics. Data associated with the participants’ evaluation of the program and their RTW processes will be collected via a survey, and from a group of approximately 40 participants. These participants were interviewed four times: at the start and end of the program and approximately 6 and 12 months after start-up.

Different methods will be used to collect data from the participating teams and key stakeholders (observations at the clinics, interviews, focus groups, and dialog meetings). For more details on the type of data collection that will be used for the process evaluation, please refer to the STAiR process protocol [51]. An overview of the outcome assessments and timing is given in the appendix.

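### The 60-month primary total counts benefit days only, so it understates absence for participants who never return to work, outlast their benefits and receive no new or increased disability pension

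*Protocol article*

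**What the plan says.** The Return to work section of the protocol article, under Primary outcome measures, lists five measures and singles out the first: "the primary outcome measure is defined as the cumulative number of sickness absence days". It is built from benefit records: "we will calculate the days on medical benefits (according to a 5-day work week) for every month during follow-up". The components named are sick-leave payment and work assessment allowance, both adjusted for employment fraction, and for pensions only change after entry: "Any increase in the disability pension during follow-up will be counted as sick leave". The totals are taken at four times: "The cumulative number of sickness absence days will be calculated at 6, 12, 24, and 60 months after inclusion". Nothing in this definition asks whether the person is at work.

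Study setting and context describes the benefits. On sick pay: "Sickness benefits are paid from the first day of absence for a period of up to 52 weeks". On what follows: "work assessment allowances or disability pensions may be granted if work ability is reduced by 50% or more". The allowances are described as coming "with a maximum duration of 3 years"; no end date is given for a disability pension.

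Table 1 requires at least 6 weeks of sick leave before inclusion and excludes people who have been out of work for more than two years.

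Work data are requested separately in Data collection: "Data regarding labor participation and employment will be collected from the State Register of Employers and Employees administered by NAV", or the equivalent from Statistics Norway. They do not enter the definition of the cumulative total.

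**The concern.** The total is presented as a measure of return to work. Benefit days track days not worked only while entitlement lasts. Once it lapses, a person who is still out of work adds zero days per month, exactly as a person back in full-time work does.

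The point at which this happens depends on how much entitlement was used before inclusion, so more days go uncounted for participants with longer prior absence. The Background names greater sick leave history as a prognostic factor for return to work. The 60-month figure could therefore be read as return to work when part of it reflects the end of entitlement. The same measure is also to be compared with a matched group from the NAV registry.

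Outcome assessment and evaluation expects no missing-data problem because the registry data are complete. Complete benefit data still do not show whether someone without a benefit is working.

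**Working it through.** The article gives no figure for benefit expiry, so there is none to reproduce. The check is calendar arithmetic on its own rules.

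**Inputs.** Sick pay lasts at most 52 weeks and the allowance at most 3 years = 156 weeks (Study setting and context). Follow-up is 60 months = 260 weeks, counted on a 5-day week (Return to work), so the maximum is 260 × 5 = 1,300 workdays. Let *u* be the weeks of benefit already used at inclusion. The minimum is taken as 6 (Table 1). Larger values of *u* are assumptions, and *u* = 104 supposes that the whole two years allowed by Table 1 were spent on benefit. Absence is assumed continuous and full, with no renewed entitlement and no new or increased disability pension.

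**Maximum cover.** 52 + 156 = 208 weeks = 48 months from the first absence day, which is less than 60 months from inclusion.

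**Allowance granted for its full term.** Cover left at inclusion = 208 − *u* weeks. Uncounted weeks by month 60 = 260 − (208 − *u*) = 52 + *u*.

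| *u* (weeks) | Cover left (weeks) | Uncounted weeks | Uncounted workdays of 1,300 | Total scored |
|---|---|---|---|---|
| 6 | 202 | 58 | 290 (22%) | 1,010 |
| 26 | 182 | 78 | 390 (30%) | 910 |
| 52 | 156 | 104 | 520 (40%) | 780 |
| 104 | 104 | 156 | 780 (60%) | 520 |

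Using exact calendar lengths instead of 52-week years gives 292, 392, 522 and 784 of 1,304, so rounding does not matter.

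**The 24-month total for the same people.** 24 months = 104 weeks. Cover left is at least 104 weeks for every *u* up to 104, so nothing is lost at 24 months.

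**No allowance granted after sick pay.** Cover left = 52 − *u* weeks.

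- *u* = 6: 46 weeks, or 230 workdays, are counted. At 12 months 260 − 230 = 30 are lost; at 24 months 520 − 230 = 290; at 60 months 1,300 − 230 = 1,070.
- *u* = 26: 26 weeks, or 130 workdays, are counted. At 12 months 130 are lost; at 24 months 390.
- At 6 months (26 weeks) nothing is lost for *u* up to 26.

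**The case against.** The strongest reply is that this is a residual group on one of several measures. Much of it stands.

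- A reader might infer that these participants are scored as not absent, or as successes. They are not. The total is cumulative and earlier benefit days remain in it: 1,010 of 1,300 with 6 weeks used, and 520 even at the two-year limit. The total is understated, not erased.
- Lasting incapacity that leads to a new or increased disability pension continues to be counted.
- The other four measures in the Return to work section rest on work status or on shifts between states and run to five years, and a multistate model is possible. A person who never returns is visible there.
- A reader might infer that the error favours one clinic. Limitations of the study attributes referral differences to patients' preferences and practical possibilities, such as family and work obligations, and does not mention prior absence. A difference between arms is possible but not shown.
- A reader might also infer that the subgroup results are biased. The Return to work section ties subgroups to this total, but Subgroup analyses names stable return to work, so that consequence cannot be asserted.
- A condensed article may leave derivation rules to a fuller document, and the definition follows a cited study that is not shown. But the article does state what is counted and when, and as stated those rules give no days to a month without benefit. If a fuller document already handles such months, citing that rule would settle the point.

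What the reply does not remove is that the measure called primary is carried to 60 months while its main components, by the article's own account, cannot last that long.

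**Conclusion.** The point holds in limited form. At 60 months, the total as defined understates absence for participants who remain out of work after sick pay and allowance end and who have no new or increased disability pension. The shortfall per person is about 290 of 1,300 workdays with 6 weeks used at inclusion, rising to about 780 if two full years on benefit came first. For participants granted no allowance, the 12- and 24-month totals can also fall short. For those who draw the full allowance, the 24-month total is unaffected.

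These are amounts per affected person under continuous full absence. They are not estimates of bias in the comparison. The number affected and any difference between the clinics cannot be derived from the article. The matter deserves a change to the outcome definition and its reporting, but it does not invalidate the study.

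**What to change.** Use the employment data already planned in Data collection to flag each month with neither registered work nor medical benefit. Report the 24- and 60-month totals in two versions: as now defined, and with flagged months counted as absence at the baseline employment fraction. A graded pension held at inclusion should not prevent a month from being flagged, because the employment fraction already allows for it. End the count at death, emigration or old-age pension in both versions, and report how many participants have flagged months in each clinic.

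Unless the two versions agree, describe the 60-month benefit-day total as benefit use, not return to work.

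A monthly flag is preferable to counting contracted days not worked. That count would be zero for anyone who no longer has a contract, and the article promises data on participation and employment, not on days worked.

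The cost is one additional derived variable and a second set of totals, once it has been confirmed what the register records by month. The drawback is that the second version also counts non-work for reasons other than health, which is why both should be shown.
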